### Patient population

The study population will be drawn from patients with a clinical diagnosis of ischemic stroke at the Emergency Department.

Patients are eligible for inclusion in DUMAS when they are 18 years or older and have a clinical diagnosis of ischemic stroke with a deficit on the National Institutes of Health Stroke Scale (NIHSS) of at least 1 point. Non-contrast computed tomography (NCCT) or magnetic resonance imaging (MRI) should rule out intracranial hemorrhage (ICH) and patients should meet the criteria for standard treatment with IV alteplase according to national guidelines [13]. Treatment should therefore be possible within 4.5 h from symptom onset or last seen well or between 4.5 and 12 h from symptom onset or last seen well, if the infarct core is less than 25 mL and the penumbra is at least the same size as the infarct core (i.e., total ischemic volume/infarct core mismatch ≥ 2.0) [14], or in case of lacunar syndrome [15], if there is a diffusion-weighted imaging (DWI) and fluid attenuation inversion recovery (FLAIR) mismatch, consistent with Dutch national guidelines for stroke [16].

Exclusion criteria are eligibility for endovascular thrombectomy (i.e., patients with a proximal large artery occlusion on CT angiography or magnetic resonance angiography), contra-indication for treatment with IV alteplase according to national guidelines, pre-stroke modified Rankin Scale (mRS) score > 2, known pregnancy, contra-indication for MRI, and participation in any therapeutic trial other than DUMAS.

There are no dropout criteria.

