### Statistical analyses

Baseline data by treatment allocation will be reported with standard statistical procedures and missing values will be reported. For regression analyses, missing values, except the primary outcome, will be imputed using multiple imputation (*n*=5). We will perform and report 4 analyses, of which the first is the primary:Simple modified intention-to-treat analysis to assess overall safety and efficacy. This is a modified intention-to-treat analysis because we exclude patients who did not give consent to participate in the study. We will additionally report safety parameters based on the full cohort, including patients who did not give consent.Targeted modified intention-to-treat analysis excluding patients with a final diagnosis other than ischemic stroke to assess safety and efficacy in the target population.Targeted modified on-treatment analysis to assess the safety and efficacy in patients who actually received treatment excluding patients with a final diagnosis other than ischemic stroke.Per-protocol analysis.

Additionally, we will perform subgroup analyses on categorized baseline variables including age, sex, systolic blood pressure, ASPECTS, time from onset to study treatment, NIHSS score, extracranial carotid or vertebral arterial occlusion, pre-study antiplatelet treatment, DWI lesion (yes/no), and lacunar syndrome (yes/no). Subgroup analyses will be done by testing for interaction of the subgroup indicator with treatment.

The effect of the study treatment on the primary outcome will be assessed with multivariable logistic regression with study treatment as a binary independent variable (m-proUK vs. control). Adjusted and unadjusted effect estimates with corresponding 95% confidence interval (CI) will be reported. The effect estimate will be adjusted for important prognostic factors at baseline, which include at least age and time from onset of symptoms to randomization. Stroke severity (NIHSS score), lacunar syndrome (yes/no) [11], systolic blood pressure, antiplatelet treatment, and endovascular treatment (yes/no) will be considered additionally in this order. Whether the dosing (initial vs. modified) of the study treatment modifies the treatment effect, will be analyzed with a multiplicative interaction parameter in the main analysis.

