### Sample size

We will include 200 patients with a final diagnosis of ischemic stroke randomized 1:1 to either standard thrombolytic treatment or dual thrombolytic treatment. We assume that the primary outcome, any ICH, will occur with a probability of 20% with standard thrombolytic treatment and a probability of 7% in the patients treated with dual thrombolytic therapy [24]. This leads to an overall effect (odds ratio (OR)) of 0.3. This sample size will provide us with a power of at least 77% to detect a statistically significant effect on the primary outcome. This estimate does not take into account the use of multivariable adjustment for differences in baseline characteristics in the primary analysis.

To ensure sufficient power in the targeted modified on-treatment analysis, an additional patient will be randomized and included (i.e., replaced) for each patient whodid not give consent for participation in the study, orfor any reason did not receive the full dose of thrombolytics as assigned, orhad a final diagnosis other than ischemic stroke (i.e., stroke mimic).◦ We estimate that up to 20% of the included patients will not have a final diagnosis of ischemic stroke [25].

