DUMAS excludes patients who are candidates for endovascular thrombectomy (i.e., patients with a proximal intracranial large artery occlusion on CTA or MRA) due to logistics with regard to other ongoing trials in this patient population in the Netherlands, and because subsequent thrombectomy will disturb the assessment of the intervention effect. However, because DUMAS allows inclusion of all other types of ischemic stroke including lacunar infarcts, cortical infarcts, and posterior circulation strokes, we expect that results will be generalizable to all patients with an indication for treatment with IV thrombolytics.

Dual thrombolytic treatment with a small bolus alteplase followed by m-proUK has the potential to be safer than standard treatment with alteplase alone, because m-proUK by itself cannot lyse hemostatic fibrin. When alteplase is cleared from the systemic circulation, hemostatic fibrin in new lesions in the ischemic region will remain intact. Therefore, this dual thrombolytic treatment is likely to reduce the occurrence of any post-treatment ICH. ICHs can be classified as either symptomatic or asymptomatic. Several classifications are in use, but symptomatic ICH is often defined as an increase in neurological deficit of 4 points or more on the NIHSS, or death, with hemorrhage confirmed by neuro-imaging. This implies that several hemorrhages may cause more subtle deterioration and are classified as asymptomatic. Moreover, it has been suggested that ICHs classified as asymptomatic are associated with worse functional outcome and should be considered relevant for functional outcome [34–36]. These considerations argue for using all intracranial hemorrhages as the primary outcome.

Moving forward to a phase 3 trial investigation, the safety and efficacy of treatment with m-proUK should be considered in case of statistically significant treatment effect on the primary outcome (i.e., any intracranial hemorrhage) or if the estimated effect is not statistically significant, but large, consistent over secondary outcomes, and in line with the pathophysiological properties of m-proUK and the experimental studies.

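### Endovascular treatment is a candidate covariate in the primary model's baseline adjustment set, although under the exclusion criteria it can only arise after randomisation

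*Protocol article*

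**What the plan says.** All references are to the protocol article.

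- **Statistical analyses, model.** "The effect of the study treatment on the primary outcome will be assessed with multivariable logistic regression", with treatment as a binary term.
- **Statistical analyses, fixed covariates.** "The effect estimate will be adjusted for important prognostic factors at baseline, which include at least age and time from onset of symptoms to randomization".
- **Statistical analyses, further candidates.** Five more follow: NIHSS score, lacunar syndrome, systolic blood pressure, "antiplatelet treatment, and endovascular treatment (yes/no) will be considered additionally in this order". EVT is the fifth.
- **Statistical analyses, reporting.** "Adjusted and unadjusted effect estimates with corresponding 95% confidence interval (CI) will be reported".
- **Sample size.** The power figure "does not take into account the use of multivariable adjustment for differences in baseline characteristics in the primary analysis". This places the adjustment inside the primary analysis and describes it as adjustment for baseline characteristics.
- **Patient population.** "Exclusion criteria are eligibility for endovascular thrombectomy", explained there as a proximal large artery occlusion on CT or MR angiography.
- **Limitations and concerns.** The exclusion is justified partly "because subsequent thrombectomy will disturb the assessment of the intervention effect".

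**The concern.** A baseline adjustment set should hold only variables fixed before randomisation. Under this trial's entry rules EVT is not one of them. No eligible patient is a thrombectomy candidate at entry, and the study drug is given directly after randomisation (SPIRIT figure legend), so a recorded EVT is a later event. The arms compare two thrombolytic regimens, so whether lysis fails or the patient deteriorates may differ by arm, and with it who goes on to EVT. EVT can also lead to ICH, which is the primary outcome.

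Conditioning on such a variable removes whatever part of the treatment effect runs through it. It can also introduce selection bias if unmeasured severity drives both EVT and ICH. The adjusted odds ratio would then not be the total effect of assignment, which is what the modified intention-to-treat primary analysis is for. The Limitations and concerns section ties the move to phase 3 first of all to a statistically significant effect on this outcome, so the primary estimate carries weight.

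**Working it through.** **1. Is EVT a baseline variable here?** Three statements have to be read together. The adjustment is for baseline factors (Statistical analyses; Sample size). EVT candidates are excluded (Patient population). The article itself regards later thrombectomy as something that disturbs the effect estimate (Limitations and concerns). In patients enrolled under these rules, EVT is either no for everyone, and so useless as a covariate, or yes because of something after randomisation. It does not fit the stated definition of the adjustment set.

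**2. The plan's own figures.** Inputs from Sample size: 20% vs 7%, 100 per arm. Two-sided alpha 0.05 is assumed, as it is not stated.

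- OR = (0.07/0.93)/(0.20/0.80) = 0.301, matching the stated 0.3.
- Power = Φ[(0.13 − 1.96·√(2·0.135·0.865/100)) / √(0.20·0.80/100 + 0.07·0.93/100)] = Φ(0.744) = 77.1%, matching the stated figure of at least 77%.

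This is an unadjusted calculation, so removing EVT from the covariates changes neither the sample size nor the stated power.

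**3. How far could the odds ratio move?** The article gives no EVT rate and no ICH rate after EVT, so every input here is an assumption. Let e be the EVT rate in an arm, h the ICH risk after EVT (same in both arms) and r the ICH risk without EVT. Then P(ICH) = e·h + (1 − e)·r in each arm, and the unadjusted OR follows from the two totals. The adjusted OR is the large-sample treatment coefficient of a logistic model with main effects for treatment and EVT.

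| EVT control / m-proUK | h | r control / m-proUK | P(ICH) control / m-proUK | Unadjusted OR | EVT-adjusted OR |
|---|---|---|---|---|---|
| 2% / 1% | 40% | 19% / 6% | 0.1942 / 0.0634 | 0.281 | 0.285 |
| 1% / 2% | 40% | 19% / 6% | 0.1921 / 0.0668 | 0.301 | 0.286 |
| 2% / 2% | 40% | 19% / 6% | 0.1942 / 0.0668 | 0.297 | 0.292 |
| 4% / 8% | 40% | 19% / 6% | 0.1984 / 0.0872 | 0.39 | 0.33 |
| 2% / 1% | 45% | 12% / 12% | 0.1266 / 0.1233 | 0.97 | 1.00 |
| 8% / 2% | 45% | 12% / 12% | 0.1464 / 0.1266 | 0.85 | 1.00 |

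Worked example, fourth row: control 0.04·0.40 + 0.96·0.19 = 0.1984; m-proUK 0.08·0.40 + 0.92·0.06 = 0.0872; unadjusted OR = (0.0872/0.9128)/(0.1984/0.8016) = 0.386. The OR is 0.272 in patients without EVT and 1.0 in those with it; the main-effects model combines these to 0.326.

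**4. A second set of assumptions.** A simulation used control ICH of 20%, a direct treatment OR of 0.30, an OR of 3 for ICH with EVT, and an unmeasured factor with ORs per SD of 2 for EVT and 1.5 for ICH. Unadjusted vs adjusted ORs were 0.314 vs 0.306 (EVT 5% / 5%, control / m-proUK), 0.297 vs 0.310 (5% / 2%) and 0.342 vs 0.301 (5% / 10%).

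The shift can go either way. It is small when EVT is rare or balanced and material when EVT is commoner and unbalanced.

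**The case against.** The strongest reply is that this will hardly matter in practice, and most of that stands.

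- The trial excludes EVT candidates, so EVT should be rare, and at 1–2% the shift is slight.
- Only age and onset-to-randomisation time are fixed. EVT is last of five candidates that are only to be considered. The design rates imply 100·0.20 + 100·0.07 = 27 events. Treatment plus all seven covariates would leave 27/8 ≈ 3.4 events per parameter, so an ordered list may well stop before EVT. That is inference, because the article gives no rule for adding or stopping.
- The unadjusted estimate is also reported, so a divergence would be visible. This limits the harm but does not cure it, since adjustment belongs to the primary analysis.
- The operative covariate list may be in the statistical analysis plan, which is not shown. The article nonetheless names the variable, its coding and its place in the order.

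Three stronger readings are tempting and are not supported.

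- A reader might infer that the odds ratio would be conditioned on a consequence of treatment. An EVT may instead follow an occlusion missed on baseline angiography, or an enrolment in breach of the exclusion. The documents support only a post-randomisation variable that treatment can affect; a mediator or collider role is possible, not shown.
- A reader might take 0.27 as the adjusted odds ratio in the 4% / 8% case. That is the odds ratio in patients without EVT; the fitted model gives 0.33.
- A reader might infer that EVT also sits in the secondary models. The article names no covariates for them beyond saying they are predictive of the outcome.

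**Conclusion.** The covariate rule is wrong as written: the set is defined as baseline factors and includes a variable that, under the trial's own exclusions, arises only after randomisation. If EVT enters the primary model, the adjusted odds ratio does not estimate the total effect of assignment. Across the assumed rates the change runs from negligible (0.281 to 0.285) to material (0.85 to 1.00, or 0.39 to 0.33), in either direction. The table is a large-sample illustration, with equal ICH risk after EVT in both arms, and does not predict this trial's data. Given the exclusion, the conditional wording and the parallel unadjusted estimate, the actual effect is probably small. Severity is moderate to low.

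**What to change.** Delete endovascular treatment from the candidate covariates of the primary model and state that adjustment sets contain only variables known before randomisation. For the secondary models this is a clarification, since no covariates are named there. Keep patients who receive EVT in the analysis as randomised, and report EVT counts by arm as a post-randomisation event. If an EVT-adjusted result is wanted, present it as a labelled sensitivity analysis.

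The cost is one line in the analysis plan, with no added patients, no new data and no change to the power calculation. The article reports that recruitment is complete, so the change should be dated and made before the unblinded analysis. If that analysis has already been run, the report should say whether EVT was in the model and show the result without it.

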### Sample size

We will include 200 patients with a final diagnosis of ischemic stroke randomized 1:1 to either standard thrombolytic treatment or dual thrombolytic treatment. We assume that the primary outcome, any ICH, will occur with a probability of 20% with standard thrombolytic treatment and a probability of 7% in the patients treated with dual thrombolytic therapy [24]. This leads to an overall effect (odds ratio (OR)) of 0.3. This sample size will provide us with a power of at least 77% to detect a statistically significant effect on the primary outcome. This estimate does not take into account the use of multivariable adjustment for differences in baseline characteristics in the primary analysis.

To ensure sufficient power in the targeted modified on-treatment analysis, an additional patient will be randomized and included (i.e., replaced) for each patient whodid not give consent for participation in the study, orfor any reason did not receive the full dose of thrombolytics as assigned, orhad a final diagnosis other than ischemic stroke (i.e., stroke mimic).◦ We estimate that up to 20% of the included patients will not have a final diagnosis of ischemic stroke [25].

### Study organization

The sponsor of the trial is the Erasmus MC University Medical Center, [name], Rotterdam, The Netherlands. The steering committee is responsible for the overall supervision of the trial. Additionally, the steering committee will discuss all patients about whom doubt exists concerning the discharge diagnosis of ischemic stroke or not (i.e., stroke mimic). Every local principal investigator can propose cases for discussion. This concerns at least patients without a DWI lesion on follow-up MRI. The executive committee keeps track of trial progress and makes the strategic decisions on a weekly basis. See the “Acknowledgements” section for a full list of the investigators.

### Ethics approval

The study will be conducted according to the principles of the Declaration of Helsinki (7th revision, Brazil, October 2013), Good Clinical Practice, the Dutch Medical Research Involving Human Subjects Act (WMO), and when it becomes applicable in accordance with regulations of other countries with participating centers. The DUMAS research protocol has been approved by the Institutional Review Board of the Erasmus MC University Medical Center (MEC-2019-0001). The current manuscript is based on protocol version 1.3.2 (April 5, 2022). The most up-to-date approved trial protocol can be found on the website (https://dumas-trial.nl/).

## Discussion

DUMAS will assess the safety and preliminary efficacy of a dual acute thrombolytic treatment consisting of a small bolus of intravenous (IV) alteplase followed by IV infusion of m-proUK against usual treatment with IV alteplase in patients presenting acutely with ischemic stroke. We hypothesize that dual thrombolytic therapy with a bolus alteplase and m-proUK will reduce the occurrence of any ICH in patients with ischemic stroke compared to patients treated with alteplase alone.

### Other ongoing trials

There are currently no other ongoing trials investigating the safety and efficacy of thrombolytic treatment with m-proUK.

There are other ongoing trials evaluating the effect of a different thrombolytic agent, tenecteplase. Tenecteplase at a dose of 0.25 mg/kg is a promising alternative to alteplase, due to its ease of administration, but until now, superiority or even non-inferiority has not been convincingly demonstrated. Also, the rates of intracranial hemorrhage in patients treated with tenecteplase and alteplase are similar [25–29].

### Limitations and concerns

As DUMAS is the first randomized clinical trial to evaluate the safety and preliminary efficacy of thrombolytic treatment with m-proUK in patients with ischemic stroke, there is no clear evidence on the most effective and safe dose of m-proUK. The m-proUK dose is based on a thrombolytic treatment with alteplase and pro-urokinase for acute myocardial infarction [10]. Previous trials that evaluated thrombolytic treatment for ischemic stroke in doses similar to those used for treatment of myocardial infarction reported high rates of ICH and no beneficial effect of treatment on functional outcome [30, 31]. That prompted investigators of thrombolytic therapy for ischemic stroke to use doses of 60% to 90% of the dose used in myocardial infarction. For example, in GUSTO, a randomized controlled trial in patients with myocardial infarction, the most effective thrombolytic regimen was accelerated tPA in a bolus of 15 mg, 0.75 mg/kg in 30 min, not to exceed 50 mg, and 0.5 mg/kg, up to 35 mg, over the next 60 min combined with intravenous heparin. This means that an average patient, weighing 75 kg, would receive a total of 100 mg alteplase (the maximum dose) [32]. The total dose used in the effective landmark alteplase trials for ischemic stroke was 0.9 mg/kg, including a 10% bolus, based on safety considerations and efficacy [2]. An average patient, weighting 75 kg, would receive a total of 67.5 mg, which comes down to 67.5% of the GUSTO dose in an average person [2, 33]. Considering the increased risk of ICH after thrombolytic treatment in patients with ischemic stroke compared with patients with myocardial infarction, the cumulative dose of pro-urokinase is reduced with 33% compared to the pro-urokinase dose given to patients with myocardial infarction [10]. Because the exact optimal dose of IV m-proUK in patients with ischemic stroke is still unknown, sequential interim analyses will be performed allowing adaptation of the IV m-proUK dose.

DUMAS excludes patients who are candidates for endovascular thrombectomy (i.e., patients with a proximal intracranial large artery occlusion on CTA or MRA) due to logistics with regard to other ongoing trials in this patient population in the Netherlands, and because subsequent thrombectomy will disturb the assessment of the intervention effect. However, because DUMAS allows inclusion of all other types of ischemic stroke including lacunar infarcts, cortical infarcts, and posterior circulation strokes, we expect that results will be generalizable to all patients with an indication for treatment with IV thrombolytics.

Dual thrombolytic treatment with a small bolus alteplase followed by m-proUK has the potential to be safer than standard treatment with alteplase alone, because m-proUK by itself cannot lyse hemostatic fibrin. When alteplase is cleared from the systemic circulation, hemostatic fibrin in new lesions in the ischemic region will remain intact. Therefore, this dual thrombolytic treatment is likely to reduce the occurrence of any post-treatment ICH. ICHs can be classified as either symptomatic or asymptomatic. Several classifications are in use, but symptomatic ICH is often defined as an increase in neurological deficit of 4 points or more on the NIHSS, or death, with hemorrhage confirmed by neuro-imaging. This implies that several hemorrhages may cause more subtle deterioration and are classified as asymptomatic. Moreover, it has been suggested that ICHs classified as asymptomatic are associated with worse functional outcome and should be considered relevant for functional outcome [34–36]. These considerations argue for using all intracranial hemorrhages as the primary outcome.

Moving forward to a phase 3 trial investigation, the safety and efficacy of treatment with m-proUK should be considered in case of statistically significant treatment effect on the primary outcome (i.e., any intracranial hemorrhage) or if the estimated effect is not statistically significant, but large, consistent over secondary outcomes, and in line with the pathophysiological properties of m-proUK and the experimental studies.

## Conclusion

DUMAS is a phase II clinical trial with PROBE design, which investigates the safety and preliminary efficacy of dual thrombolytic treatment consisting of a small bolus alteplase followed by m-proUK IV infusion against usual treatment with alteplase in patients presenting with ischemic stroke. When this dual thrombolytic therapy with a small bolus alteplase and m-proUK shows the anticipated effect on outcome, this will lead to a 13% absolute reduction in the occurrence of ICH in patients with ischemic stroke.

